### Quality control

All researchers will take a training course before the beginning of this trial. Due measures will be implemented to ensure the traceability and confidentiality of the case report form, informed consent form, and other original data. A double-input method will be used for data entry. AEs will be recorded in detail, properly handled, and tracked. All trial-related procedures and data management will be supervised. The Data Monitoring Committee of the Guang’anmen Hospital will regularly monitor the recruitment and screening of participants, data collection, monitoring, and verification of AEs to ensure that the study is conducted in accordance with the approved protocol.

## Discussion

AV is a common chronic inflammatory dermatologic disease. It may affect the physical and mental health of patients and may adversely affect their QoL [34]. According to an epidemiological study, approximately 20% of young people are affected by moderate to severe AV [35]. Several studies have demonstrated a correlation between the QoL and the severity of dermatologic disease [36]. For this reason, this study will only include participants with moderate or severe AV.

The primary outcome of the study will be the Skindex-16 scale score. It is a validated and sensitive scale to measure the QoL of patients with dermatologic diseases [20, 21]. Because lesions of AV mainly occur on areas of the face and are accompanied by other symptoms of itch and pain [32, 33], patients tend to present with psychosocial symptoms and impaired QoL. The Skindex-16 scale consists of 16 questions in the symptoms, emotion, and function domains; responses to each question are scored on a 7-point Likert scale [20, 21]. This scale includes seven questions related to the symptoms (itch or pain) and characteristics (lesions) of AV. It is a sensitive and specific tool to assess the symptoms and QoL of patients with moderate or severe AV. Moreover, we also used the DLQI scale to evaluate QoL. It is a brief, skin-related QoL scale with satisfactory reliability and validity, and it was used to further evaluate the effectiveness of acupuncture in improving the QoL of patients with AV [29]. In addition, TLC, ILC, IVAS, and PVAS will also be used as secondary outcomes to assess the lesion counts and main symptoms (itch or pain) related to AV. These would provide a comprehensive evaluation of the overall effectiveness of acupuncture.

In this trial, we aim to evaluate the therapeutic effect of acupuncture on the symptoms and QoL of patients with moderate or severe AV. The possible placebo effects of acupuncture may be attributable to the participants’ expectations of acupuncture; the degree of trust between the acupuncturist and the participant; and any difference in the type, frequency, or course of the intervention of acupuncture [37, 38]. To partially exclude the placebo effects and demonstrate the real effect of acupuncture, we plan to use sham acupuncture as a comparator.

The sham acupuncture is a crucial tool that can minimize participants’ expectations and the bias of both participants and researchers and assist in the enforcement of blinding [38]. Use of the non-insertion-type needle on nonacupoints was shown to be an optimal method to reduce the possible biological effects [39]. However, the non-insertion-type needle leaves no marks or wounds on the skin. In this condition, the lack of any needle marks may compromise the blinding of participants. Therefore, we will opt for nonacupoints and minimal acupuncture as the sham acupuncture in this trial. Nonacupoints are in proximity to the classical acupoints, which will increase the feasibility of blinding [38]. Meanwhile, using the nonacupoints and minimal acupuncture without any manipulation may minimize actual needle sensation to mitigate the potential physiologic stimulus [38, 40]. The outcome assessors of this study will be blinded to the group allocation, which will also mitigate the lack of acupuncturist blinding.

However, some limitations of our study should be acknowledged. First, the single-center scope of the study and the relatively small sample size may lead to overestimation of the effects of acupuncture. Second, because of the characteristics of acupuncture, the acupuncturist will not be blinded in our trial, which may cause potential bias. Last, it is difficult for the sham acupuncture to be as inert as desired in this trial, owing to a slight stimulus or a stronger stimulus of gentle touch possibly leading to different degrees of neurological responses related to the treatment effect [39, 41]. So, the use of nonacupoints and minimal acupuncture without any manipulation may cause some biological effect leading to false-negative results [36].

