Several trials have indicated that acupuncture may alleviate the skin lesions and improve the QoL of patients with AV [11–15]. However, these trials were affected by potential bias due to small sample sizes, nonplacebo/sham/waiting list control, or use of self-defined outcome measures; thus, they did not provide robust evidence of the efficacy of acupuncture in patients with AV. Therefore, we conducted a pilot trial (unpublished) from April 2017 to March 2018 in which 42 patients with moderate or severe AV were randomly allocated to an acupuncture group (*n* = 21) or a sham acupuncture group (*n* = 21). After a 4-week treatment, the number of inflammatory lesions in the acupuncture group (*n* = 21) was 35.62 ± 15.51, with a reduction of 6.62 ± 15.42 from baseline. The number of inflammatory lesions in the sham acupuncture group (*n* = 21) was 30.05 ± 21.16, with a reduction of 15.10 ± 20.13 from the baseline. The difference between the two groups was 8.48 ± 7.74, and there was no significant between-group difference with the *p* = 0.137 due to *p* > 0.05 was considered nonsignificant. These findings contradict the results of previous trials [11–14], and authors of a systematic review of AV also reported that there was no difference between acupuncture and the waiting list for reducing the number of inflammatory lesions [16]. Unlike drugs, which act directly on the pathogen, acupuncture restores normal functions through motivating or inducing the inherent regulatory system [17]. Therefore, acupuncture may relieve other symptoms of AV (itch or pain) [18, 19] and improve the QoL [11]. The Skindex-16 scale is a sensitive and specific tool for assessing the symptoms and QoL of patients with AV, and it includes seven questions related to the symptoms (itch or pain) and characteristics (skin lesions) of AV [20, 21]. Following the 4-week treatment, the total score on the Skindex-16 scale for acupuncture (*n* = 21) was 19.89 ± 15.40, with a reduction of 12.50 ± 19.09 from the baseline. The total score on the Skindex-16 scale for sham acupuncture (*n* = 21) was 30.43 ± 19.39, with a reduction of 0.40 ± 21.12 from the baseline. The difference between the two groups was − 12.9 ± 11, and there was a significant between-group difference in this instance with the *p* = 0.044 due to *p* < 0.05 was considered statistically significant. Therefore, the results of our pilot study indicated that acupuncture may help to relieve total symptoms and improve the QoL of patients with moderate or severe AV. So far, there are two systematic reviews that recommend using the measure of QoL for evaluating the effect of acupuncture on AV [10, 16], but no clinical trials have been conducted that use the measure of QoL to evaluate the effect of acupuncture on the symptoms and the QoL of patients with AV. Therefore, we intend to use the Skindex-16 scale as a primary outcome measure in our planned study to evaluate the effect of acupuncture compared with sham acupuncture on the symptoms and QoL of patients with moderate or severe AV.

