### Study recruitment

Participants will be recruited between August 2019 and December 2020 at the Guang’ anmen Hospital via advertisements on posters, the WeChat app, and hospital websites. A dermatologist will be responsible for the screening, which will include diagnosis of the type of acne of patients and a series of physical examinations (discrimination between inflammatory and noninflammatory lesions of AV by the pictures of participants’ faces obtained using a digital camera) according to the diagnostic criteria for AV [2, 24] and the classification of lesions of AV [25], respectively.

All participants will be asked by a research assistant to read the informed consent form that describes the trial, randomization process for treatments, and the potential benefits and risks of the trial. Participants will be informed that both acupuncture and sham acupuncture may be effective for AV, and they will be randomly assigned to the acupuncture group or the sham acupuncture group. Participants will be allowed to withdraw from the trial at any time. Written informed consent will be obtained from all subjects prior to their enrollment.

The demographic and clinical characteristics of the participants at baseline will be recorded by a research assistant: age, sex, race, body mass index (in kg/m^2^), marital status, education level (primary education or below, secondary education, and tertiary education), time of sports activity (0–3 times/month, 1–2 times/week, 3–4 times/week, and ≥ 5 times/week), daily sleep duration (< 7 h, 7–9 h, and > 9 h), smoking history, history of alcohol intake, AV duration in months, and severity of AV as assessed by Global Acne Grading System (GAGS) score (none [0 score], mild [1–18 score], moderate [19–30 score], severe [31–38 score], and markedly severe [> 39 score]) [26].

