### Acupuncture group

The location of acupoints is described as per the Nomenclature and Location of Acupuncture Points (National Standard of People’s Republic of China, 2006 [GB/T 12346-2006]) [27]. The selection of acupoints will be decided with reference to the Guidelines for AV treatment in China (revised version 2014) [28]. Participants in the acupuncture group will receive stimulation at Dazhui (CV14), bilateral Quchi (LI11), bilateral Hegu (LI4), bilateral Zusanli (ST36), and bilateral Neiting (ST44) with disposable acupuncture needles (0.30 × 40 mm, Huatuo Brand; Suzhou Medical Appliance, Suzhou, Jiangsu, China). After routine disinfection, acupuncture needles will be inserted obliquely into CV14 to a depth of 30–40 mm at an angle of 15–30 degrees; acupuncture needles will be vertically inserted into bilateral LI11, bilateral LI4, bilateral ST36, and bilateral ST44 to a depth of 25–30 mm three times (once every 10 min) with slight lifting, thrusting, and twisting manipulations to produce a sensation of de-qi. Each session of acupuncture will last 30 min.

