### Sham acupuncture group

Participants in sham acupuncture group will receive sham acupuncture at sham CV14 (10 mm to CV14), LI11 (10 mm to LI11), LI4 (10 mm to LI4), ST36 (25 mm to ST36), and ST44 (10 mm to ST44) with disposable acupuncture needles (0.30 × 25 mm, Huatuo Brand). Sham CV14, LI11, LI4, ST36, and ST44 will be vertically inserted to a depth of 1–2 mm without any manipulation and de-qi. The treatment sessions will last 30 min.

Participants will not be allowed use of other treatments for AV throughout the trial. Detailed information pertaining to use of other treatments will be recorded in the case report form.

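### People who already know the feel of real needling, including the 42 pilot participants, may enter without that experience being listed at baseline, and they may be more easily unblinded

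*Protocol article*

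**What the plan says.** **Eligibility.** The last exclusion criterion removes people who had acupuncture in the preceding 3 months. There is no lifetime restriction and no bar on participants of an earlier trial.

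**Pilot.** The Background reports a randomised pilot of acupuncture against sham, run "from April 2017 to March 2018 in which 42 patients with moderate or severe AV were randomly allocated". Each arm had 21 patients and treatment lasted 4 weeks. For the present trial, "Participants will be recruited between August 2019 and December 2020".

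**Baseline data.** Study recruitment states that "The demographic and clinical characteristics of the participants at baseline will be recorded by a research assistant" and then itemises them, down to marital status, sports frequency and sleep duration. Earlier acupuncture is not on the list. The two baseline questions under Secondary outcomes ask what participants expect of acupuncture, not whether they have had it.

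**The arms.** Real needles go 25–30 mm deep at four bilateral points and 30–40 mm obliquely at the fifth, "with slight lifting, thrusting, and twisting manipulations to produce a sensation of de-qi". Sham needles go "to a depth of 1–2 mm without any manipulation and de-qi".

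**Blinding.** The Blinding section declares participants blinded and asks one question in week 4, answered yes, no or unclear. The Discussion gives two blinding reasons for this sham: inserted needles leave marks, and "Nonacupoints are in proximity to the classical acupoints, which will increase the feasibility of blinding". It gives reduced sensation a different purpose: "using the nonacupoints and minimal acupuncture without any manipulation may minimize actual needle sensation to mitigate the potential physiologic stimulus".

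**The concern.** Needle marks and nearby points help to keep the arms looking alike. They do not make them feel alike, and the protocol deliberately makes them feel different. A participant who has felt de-qi before has a standard of comparison that a first-time participant lacks. The 3-month rule limits carry-over from recent treatment but does nothing about memory of the sensation.

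The primary outcome is the change in Skindex-16 total score, a quality-of-life scale, so blinded outcome assessors give it limited protection and participant blinding matters most. The Discussion itself names participants' expectations as a source of placebo effect. If experienced participants on sham recognise it and report less benefit, or those on real acupuncture recognise that and report more, the difference moves in favour of acupuncture. The Discussion's sham-specific limitation concerns the opposite direction, a false-negative result from a sham that is not inert.

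If earlier acupuncture is not recorded before randomisation, the week-4 answers cannot be split by it, and history collected later would rest on recall that the trial treatment may have coloured.

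**Working it through.** The document gives no figure for this point, so there is none to reproduce. The check is a reading of the rules, a date calculation and an illustration.

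**1. Does the exclusion rule catch the pilot participants?** From the end of March 2018 to the start of August 2019 is 9 months (April to December 2018) + 7 months (January to July 2019) = 16 months. To the end of recruitment in December 2020 it is 16 + 17 = 33 months. If March 2018 marked the last enrolment rather than the last treatment, the 4-week course would shorten the gap by about one month, to 15. Every value is well beyond 3 months, so pilot treatment bars none of the 42. They were also in the severity range sought now, moderate or severe acne.

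**2. Is the experience captured?** The baseline list omits it, the expectation questions do not ask for it, and the outcome timetable (Table 1) has no such item.

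**3. Can the arms be told apart by feel?** Depth is 25–30 mm (30–40 mm oblique at one point) against 1–2 mm; manipulation three times per session against none; de-qi sought against not sought.

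**4. Illustrative size (assumptions, not document figures).** Let *f* be the share of participants who are unblinded and *b* the number of points by which unblinding widens the arm difference among them. Then bias = *f* × *b*. For the effect on the type I error, assume no true effect and 50 × 0.8 = 40 completers per arm. The SD is pooled from the pilot figures in the sample size section:

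- SD = √((19.09² + 21.12²)/2) = 20.13
- SE = 20.13 × √(2/40) = 4.50
- Type I error = Φ(bias/SE − 1.96) + Φ(−bias/SE − 1.96)

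| *f* | *b* | Bias (points) | Bias/SE | Type I error |
|---|---|---|---|---|
| 10% | 5 | 0.5 | 0.11 | 5.1% |
| 20% | 10 | 2.0 | 0.44 | 7.3% |
| 42% | 10 | 4.2 | 0.93 | 15.4% |

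The last row needs all 42 pilot participants to return and all to be unblinded, which is an extreme bound. For scale, the difference implied by the sample size section is 12.50 − 0.40 = 12.1 points, and the stated MCID is 10.

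**5. What could an analysis of never-needled participants show?** If 60% had earlier acupuncture (assumed), 50 × 0.4 = 20 per arm remain, or 16 after 20% dropout. With a difference of 12.1 and SD 20.13, the two-sided 5% *t*-test has power of about 46% or 38%. A null result there could not separate unblinding from imprecision.

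**The case against.** The strongest reply is that nothing here is an error. Admitting people with past acupuncture is a legitimate eligibility choice, no figure is wrong and no passages conflict. The article is condensed and the case report form is not shown; applying the 3-month rule already requires asking about recent needling, so earlier treatment may well be noted. Safeguards exist too: the week-4 question with a chi-square test, consent wording that either treatment may be effective, separate treatment of participants, and baseline expectations. Re-entry from the pilot needs a qualifying severity score again and none of the excluded drugs in the preceding month, and half of the pilot patients received sham.

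Much of this stands. The safeguards are real and would show material unblinding from any cause, but they detect or soften it rather than prevent it, and without the history its source could not be examined. That the item is unrecorded can be said only of the published list.

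Three stronger readings are tempting and not supported:

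- A reader might infer that the Discussion rests blinding on minimised needle sensation. It ties that to physiologic stimulus; its blinding reasons are needle marks and nearby points.
- A reader might infer that pilot participants learned their allocation. The document does not say so, and it does not describe the pilot's site or sham technique.
- A reader might take the bias figures as estimates. Every value of *f* and *b* is assumed, and at the low end the effect is negligible.

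**Conclusion.** The point holds as a modest, cheaply remedied weakness in a stated eligibility rule and an itemised baseline list. People who know real needling, including all 42 pilot participants as far as acupuncture history goes, may enter; the published baseline list would not identify them; and the contrast between the arms may make them easier to unblind on a quality-of-life primary outcome. The document does not show that blinding will fail. The number affected and the size of any bias cannot be derived from it; the 0.5 to 4.2 points above are illustrative and depend wholly on the assumed *f* and *b*, on 40 completers per arm and on the pilot SD. The case for acting rests on the low cost before recruitment starts, not on a demonstrated bias.

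**What to change.** 1. **Exclusion criteria:** add participation in the pilot trial.
2. **Study recruitment, baseline list:** add one item, completed before randomisation: ever had acupuncture (yes/no) and date of last session. If the case report form already holds it, add it to the published list.
3. **Sample size and statistical analysis:** report the week-4 blinding answers by arm within levels of that item, and present the primary outcome by prior experience as a supportive, exploratory analysis, stating that its power is low. The primary analysis is unchanged.

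The cost is a few potential recruits from the pilot, one form item and one additional table. The Trial status section reports no recruitment at present, so the changes can be made before the first participant enters.

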### Trial status

No recruitment currently.

## Data Availability

All relevant data will be shared for a period beginning 3 months after publication and ending 5 years after publication.

## Abbreviations

AE: Adverse event
AV: Acne vulgaris
DLQI: Dermatology Life Quality Index
GAGS: Global Acne Grading System
ILC: Inflammatory lesion count
IVAS: Itch Assessment with Visual Analogue Scale
MCID: Minimal clinically important difference
PVAS: Pain Assessment with Visual Analogue Scale
QoL: Quality of life
SPIRIT: Standard Protocol Items: Recommendations for Interventional Trials
STRICTA: Standards for Reporting Interventions in Clinical Trials of Acupuncture
TLC: Total lesion count
